##### Process measures

Several process measures are collected at 5 weeks regarding engagement with and perceived usefulness of each allocated resource (i.e. MOOC or electronic OA information pamphlet). Table 2 lists all process measures.

### Data analysis, monitoring and auditing

#### Sample size calculation

A sample size of 60 participants per arm (120 in total) is required for 90% power to demonstrate that the consumer-facing MOOC is superior to the control with a two-sided 2.5% significance level (accounting for multiple comparisons across the two primary outcomes by using Bonferroni correction) and allowing for a 20% dropout rate. The sample size calculation was based on the following assumptions: a standardised between-group effect size of 0.625 for pain self-efficacy (based on our prior research [31], corresponding to an absolute between-group difference in mean change from baseline to 5 weeks of 1 unit in ASES pain subscale score favouring the MOOC, with within-group standard deviation (SD) of 1.6 units [31], correlation between measures across all three timepoints of 0.5 (i.e., compound symmetry variance–covariance matrix) [31], and using a constrained longitudinal data analysis (cLDA) model [32]. With this sample size, we also have at least 90% power to detect a between-group effect size of 0.8 for OA knowledge (conservative for this type of program [33]), corresponding to an absolute between-group difference in mean change from baseline to 5 weeks of 4.6 units in KOAKS/HOAKS score favouring the MOOC, with within-group SD of 5.8 units [31], and correlation between measures across all three timepoints of 0.2 [31].

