Our team has developed the first consumer-facing MOOC about OA and its management, for people with OA, which we aim to evaluate in this trial. Our primary hypothesis is that people with hip and/or knee OA who receive the 4-module 4-week MOOC will have greater improvements in OA knowledge and/or self-efficacy for pain at 5 weeks compared to those who receive a typical OA education intervention: an electronic OA information pamphlet available from a reputable consumer organisation. Our secondary hypothesis is that those receiving the MOOC will have more favourable changes in a range of other outcomes including fear of movement, exercise self-efficacy, illness perceptions, OA management and health professional care seeking intentions, physical activity levels, and actual use of physical activity/exercise and weight loss, pain medication, and health professional care seeking to manage joint symptoms.

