### Randomisation and blinding

Participants are enrolled into the study on completion of baseline questionnaires and are randomised (1:1 ratio) into one of two groups i) electronic OA information pamphlet (control group) or ii) MOOC (experimental group), using randomly permuted blocks of varying sizes, stratified by eligible joint (hip or knee). The randomisation list was computer-generated by an independent statistician and is managed by a researcher centrally to ensure concealment. Participants are blinded to group allocation using limited disclosure (told that the study is investigating two different types of information material about OA but without explicit detail about either intervention nor the study hypotheses given). As primary outcomes are participant-reported, and participants are blinded, by default the assessors of these outcomes are blinded. Statistical analyses will be performed while blinded.

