#### Data analysis

The biostatisticians (FM, [name], [name]) will devise a statistical analysis plan for the study prior to being unblinded to group allocation. It will be published on our Centre’s website. Analyses will include all participants according to their group allocation (intention-to-treat). Each primary outcome will be analysed using a cLDA [32] model. The response will consist of all KOAKS/HOAKS or ASES pain scores (at baseline, 5 and 13 weeks), and the model will include factors for group, time (categorical), and group-by-time interaction, with the restriction of a common baseline mean across treatment groups. The mean change in KOAKS/HOAKS or ASES pain scores from baseline to each follow-up timepoint between the groups will be obtained. The primary hypothesis will be evaluated by obtaining the estimated differences between groups in mean change in KOAKS/HOAKS and ASES pain score from baseline to 5 weeks post randomisation, and multiplicity adjusted two-sided 95% confidence intervals and *p*-values. These models provide valid inference in the presence of missing data if the data are missing at random (MAR). An analysis will be conducted using the delta-adjustment method under the pattern-mixture modelling framework in the context of multiple imputation to assess sensitivity to missingness not at random. Secondary outcomes: Management intentions and care seeking intentions at 5 weeks, and care seeking behaviour, exercise and weight loss behaviours and pain medication usage (adjusted for baseline usage) at 13 weeks will be analysed using log-binomial regression models. Physical activity levels at 13 weeks will be analysed using a linear regression model adjusted for baseline physical activity. Other continuous outcomes will be analysed the same as the primary outcomes. All analysis models will be adjusted for the stratification factor, eligible joint (hip/knee). Process measures and other baseline measures will be summarised using frequency (proportion) for binary measures and mean (SD)/ median (inter-quartile range) for continuous measures.

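### Bonferroni at 2.5% per primary outcome is valid and adequately powered, but Holm-adjusted p-values would add power on each outcome within the same 5% family-wise limit

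*Protocol article*

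**What the plan says.** The Sample size calculation section works "with a two-sided 2.5% significance level", explained as "accounting for multiple comparisons across the two primary outcomes by using Bonferroni correction". On that basis it states: "A sample size of 60 participants per arm (120 in total) is required for 90% power", "allowing for a 20% dropout rate". Pain self-efficacy drives the number. OA knowledge is said to have at least 90% power at the same size.

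The Data analysis section says that the primary hypothesis will be judged on the 5-week differences in mean change, with "multiplicity adjusted two-sided 95% confidence intervals" and p-values. It does not name the adjustment. It leaves further detail to a statistical analysis plan to be written before the biostatisticians are unblinded.

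The primary hypothesis in the Background is satisfied by either outcome or both: the MOOC group "will have greater improvements in OA knowledge and/or self-efficacy for pain at 5 weeks".

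**The concern.** Single-step Bonferroni tests each outcome at 2.5% whatever happens on the other. Holm tests the smaller p-value at 2.5% and, if that is significant, tests the other at 5%. It needs no assumption about how the outcomes are correlated and no extra participants.

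The plan assumes a larger standardised effect for OA knowledge (0.8) than for pain self-efficacy (0.625). If those assumptions hold, OA knowledge will usually be significant first. Bonferroni would then still hold pain self-efficacy, the outcome that sized the trial, to 2.5%. A pain self-efficacy p-value between 0.025 and 0.05 would be called non-significant, although a procedure with the same 5% family-wise guarantee would accept it.

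**Working it through.** **Inputs, all from Sample size calculation unless noted.** Two-sided alpha 0.025 per outcome; power 90%; dropout 20%; 1:1 allocation (Randomisation and blinding). Pain self-efficacy: difference 1, SD 1.6, correlation between timepoints 0.5. OA knowledge: difference 4.6, SD 5.8, correlation 0.2. The correlation between the two test statistics is not given; 0, 0.3, 0.5 and 0.8 are assumed.

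**Step 1: reproduce the sample size.** With a common baseline mean, the constrained longitudinal model reduces the variance by the factor 1 − r². For pain self-efficacy:

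n per arm = 2(2.2414 + 1.2816)² × (1 − 0.25) / 0.625² = 47.7, so 48. Then 48 / 0.8 = 60.

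The stated 60 per arm reproduces. Without the baseline gain the result is 64, or 80 after dropout, which does not.

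**Step 2: power under Bonferroni at 48 completers per arm.** Expected z = difference / (SD × √(1 − r²) × √(2/48)).

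- Pain self-efficacy: 1 / (1.6 × √0.75 × √(2/48)) = 3.54. Power = Φ(3.54 − 2.24) = 90.2%. At a 5% level it would be 94.2%.
- OA knowledge: 4.6 / (5.8 × √0.96 × √(2/48)) = 3.97. Power = Φ(3.97 − 2.24) = 95.8%. At a 5% level it would be 97.8%.

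Both power statements in the plan are met.

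**Step 3: power under Holm.** An outcome is significant if it passes at 2.5%, or if it passes at 5% and the other passes at 2.5%. With independent statistics:

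- Pain self-efficacy: 0.902 + (0.942 − 0.902) × 0.958 ≈ 0.941.
- OA knowledge: 0.958 + (0.978 − 0.958) × 0.902 ≈ 0.976.

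Simulation with 2 million bivariate normal draws per setting gives, in percent:

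| Assumed correlation | Pain self-efficacy, Holm | OA knowledge, Holm | Both, Bonferroni | Both, Holm | At least one, either method |
|---|---|---|---|---|---|
| 0 | 94.11 | 97.55 | 86.43 | 92.07 | 99.59 |
| 0.3 | 93.91 | 97.30 | 87.03 | 92.26 | 98.95 |
| 0.5 | 93.77 | 97.10 | 87.70 | 92.54 | 98.33 |
| 0.8 | 93.57 | 96.51 | 89.05 | 93.17 | 96.91 |

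**Step 4: error rates.**

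- Neither effect real: family-wise error is the same under both methods, 4.9% falling to 4.0% as the correlation rises from 0 to 0.8.
- One effect real: the error on the null outcome is 2.5% under Bonferroni and 4.1% to 4.9% under Holm. For example, with OA knowledge real and independence, 0.025 + 0.025 × 0.958 = 4.9%. Power on the real outcome rises by about 0.2 points or less.

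**Step 5: how often p-value and interval would disagree.** This happens exactly when Holm adds a second rejection, so its frequency is the gap between the two columns for both outcomes: 92.07 − 86.43 = 5.6% of trials at correlation 0, and 93.17 − 89.05 = 4.1% at 0.8.

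**The case against.** The strongest reply is that nothing here is wrong. Bonferroni controls the family-wise error, matches the sample size, meets the stated power on both outcomes, and supplies the promised adjusted intervals directly, as 97.5% intervals that always agree with the tests. All of that stands. The point is an efficiency gain, not an error or a contradiction.

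A reader might infer four stronger things that the protocol does not support:

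- **That the analysis is fixed as Bonferroni.** The method is named only for sizing. The Data analysis section names none, and the statistical analysis plan, which is not shown, may already specify Holm. Bonferroni in the analysis is the natural reading, not an explicit rule.
- **That Holm costs nothing.** It has no equally simple matching simultaneous intervals. With Bonferroni intervals alongside, an outcome can be declared significant while its interval includes zero. A team that values agreement between the two could reasonably stay with Bonferroni.
- **That the error rate is identical.** It is identical only when neither effect is real. If the course improves knowledge alone, Bonferroni keeps the error on pain self-efficacy at 2.5%, while Holm lets it approach 5%.
- **That the primary hypothesis gains power.** It needs only one outcome, and Holm's first step is the Bonferroni test, so power for at least one outcome does not move. The protocol sets no requirement to win on both.

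**Conclusion.** The point holds as a cheap improvement. If Bonferroni is carried into the analysis, it gives up about 3.3 to 3.9 points of power on pain self-efficacy, 0.8 to 1.8 points on OA knowledge and 4 to 6 points on winning both, compared with a test that meets the same 5% family-wise limit.

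These gains assume that both effects are real at the planned sizes, 48 completers per arm, a normal approximation, and a correlation of 0 to 0.8 between the test statistics, which the protocol does not give. The gain matters for what can be claimed about each outcome separately; it does nothing for the either-or-both hypothesis. The sample size itself is sound.

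**What to change.** Before unblinding, add one sentence to the Data analysis section or the statistical analysis plan: the p-values for the two primary outcomes at 5 weeks are Holm-adjusted (smaller p-value tested at 2.5% and, if significant, the other at 5%), and each estimate is reported with a 97.5% Bonferroni simultaneous confidence interval. Add that the interval for the second outcome can include zero while its Holm-adjusted p-value is below 0.05, and that this will be noted in the report if it occurs.

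No extra participants, data or change to the model are needed. The present sample size stays as a conservative calculation. The cost is the possible disagreement just described, in about 4 to 6% of trials under the plan's assumptions, and the higher error on a null outcome when the other effect is real. If the team prefers tests and intervals that always agree, it should state explicitly that Bonferroni applies to the analysis as well as to the sizing.

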#### Data analysis

The biostatisticians (FM, [name], [name]) will devise a statistical analysis plan for the study prior to being unblinded to group allocation. It will be published on our Centre’s website. Analyses will include all participants according to their group allocation (intention-to-treat). Each primary outcome will be analysed using a cLDA [32] model. The response will consist of all KOAKS/HOAKS or ASES pain scores (at baseline, 5 and 13 weeks), and the model will include factors for group, time (categorical), and group-by-time interaction, with the restriction of a common baseline mean across treatment groups. The mean change in KOAKS/HOAKS or ASES pain scores from baseline to each follow-up timepoint between the groups will be obtained. The primary hypothesis will be evaluated by obtaining the estimated differences between groups in mean change in KOAKS/HOAKS and ASES pain score from baseline to 5 weeks post randomisation, and multiplicity adjusted two-sided 95% confidence intervals and *p*-values. These models provide valid inference in the presence of missing data if the data are missing at random (MAR). An analysis will be conducted using the delta-adjustment method under the pattern-mixture modelling framework in the context of multiple imputation to assess sensitivity to missingness not at random. Secondary outcomes: Management intentions and care seeking intentions at 5 weeks, and care seeking behaviour, exercise and weight loss behaviours and pain medication usage (adjusted for baseline usage) at 13 weeks will be analysed using log-binomial regression models. Physical activity levels at 13 weeks will be analysed using a linear regression model adjusted for baseline physical activity. Other continuous outcomes will be analysed the same as the primary outcomes. All analysis models will be adjusted for the stratification factor, eligible joint (hip/knee). Process measures and other baseline measures will be summarised using frequency (proportion) for binary measures and mean (SD)/ median (inter-quartile range) for continuous measures.

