**Table 2 Tab2:**
[figure not shown]
Schedule of enrolment, intervention, and assessments [22, 23]

*MOOC* Massive Open Online Course, *WOMAC* Western Ontario and McMaster Universities Osteoarthritis Index, *BMI* Body Mass Index, *OA* osteoarthritis, *NRS* Numeric rating scale

^*^via 4-point Likert scale with terminal descriptors 1 = not at all confident; 4 = extremely confident

^#^via a 4-point Likert with response options none, a little, some, a lot

^via Yes/No response to both “For your osteoarthritis, are you currently making efforts to i) lose weight (e.g. dietary changes) ii) increase the amount/intensity of physical activity/exercise you do?”

^¶^Yes/No response to “Have you ever sought care for your knee or hip pain from any health professional before?”

^§^Yes/No response to “In the past month, have you seen a health professional for advice about your osteoarthritis?” Those selecting “Yes” will be asked which health professionals they have seen

^$^via 4-point Likert scale with response options: 1 = not at all useful; 2 = slightly useful; 3 = moderately useful; 4 = extremely useful. Dichotomised into useful (slightly, moderate, extremely) and not useful (not at all useful)

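### Week-13 weight-loss behaviour, and the week-5 intentions to lose weight and to be more active, could be adjusted for baseline effort items that the trial appears to collect already

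*Protocol article*

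**What the plan says.** The Data analysis section puts the week-5 intentions and the week-13 care-seeking, exercise, weight-loss and medication outcomes into log-binomial models. Within that list it states that "exercise and weight loss behaviours and pain medication usage (adjusted for baseline usage) at 13 weeks will be analysed using log-binomial regression models". The bracketed adjustment refers to usage, so it is read as belonging to pain medication alone. The same section adjusts week-13 IPEQ-W for its baseline value, uses baseline through the cLDA model for the other continuous outcomes, and adds eligible joint to every model. The remaining baseline measures are given only a descriptive summary.

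The Table 2 footnotes give a yes/no item that asks, in respect of the participant's osteoarthritis, "are you currently making efforts to i) lose weight (e.g. dietary changes) ii) increase the amount/intensity of physical activity/exercise you do". The Secondary outcome measures section defines week-13 weight-loss behaviour as a yes/no answer on any effort to lose weight in the preceding fortnight. It defines two of the week-5 intentions as yes/no answers on increasing activity and on trying to lose weight over the following two months.

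**The concern.** The plan uses baseline for two of the outcomes in these regressions and not for weight loss, although the Table 2 item and the week-13 question ask almost the same thing in the same yes/no form. The two effort items are also natural predictors of the corresponding intentions: someone already trying to lose weight or be more active is in a different position when asked whether they intend to.

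At stake are the precision of three secondary estimates and their exposure to chance imbalance. Randomisation is stratified by joint only, so baseline effort can differ between arms by chance, and an unadjusted risk ratio carries that difference. The primary outcomes are not affected.

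**Working it through.** **1. The plan's own figure.** Inputs from the Sample size calculation section: "A sample size of 60 participants per arm (120 in total) is required for 90% power", "with a two-sided 2.5% significance level", "allowing for a 20% dropout rate", a difference in "mean change from baseline to 5 weeks of 1 unit in ASES pain subscale score", "with within-group standard deviation (SD) of 1.6 units", and correlation 0.5.

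- Residual variance after using baseline: 1.6² × (1 − 0.5²) = 2.56 × 0.75 = 1.92.
- n per arm = 2 × (2.241 + 1.282)² × 1.92 / 1² = 47.7, so 48; 48 / 0.8 = 60. The stated 60 per arm reproduces.
- Without the baseline correlation, n per arm = 2 × (3.523)² × 2.56 = 63.5, so 64.

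The plan therefore already relies on baseline information for its primary outcome. It leaves 48 expected completers per arm.

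**2. Are the effort items baseline items?** The Table 2 grid is not shown. The items are not among the outcomes defined in the Secondary outcome measures section, and the Outcomes section says Table 2 holds the baseline descriptive data as well as the outcomes. Baseline timing is a reasonable inference, not a verified fact.

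**3. Precision gain.** The protocol gives neither the prevalence of these behaviours nor their correlation φ with baseline, so both are assumed. On the linear scale, the adjusted-to-unadjusted variance ratio is 1 − φ²:

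| φ (assumed) | 1 − φ² | CI width multiplier | Equivalent n per arm, 48/(1 − φ²) |
|---|---|---|---|
| 0.2 | 0.96 | 0.98 | 50 |
| 0.3 | 0.91 | 0.95 | 53 |
| 0.4 | 0.84 | 0.92 | 57 |
| 0.5 | 0.75 | 0.87 | 64 |

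**4. Check by simulation with a regression model.** Settings: 48 per arm, risk ratio 1.5, robust Poisson, 1,500 trials per scenario, half the participants with the baseline behaviour. With both margins near 50%, φ is the difference between the two conditional percentages. Later behaviour of 60% against 40% by baseline status is thus φ = 0.2, and 75% against 25% is φ = 0.5. Variance ratios for the log risk ratio were 1.00, 0.97, 0.92, 0.86 and 0.78 at φ = 0.1, 0.2, 0.3, 0.4 and 0.5. With 20–30% prevalence and a modest association they were 0.99 to 1.01.

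Two separate sets of runs agreed on variance but less well on power at two-sided 5%:

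- φ = 0.3: 50% to 51%, and 53% to 57%
- φ = 0.4: 52% to 54%, and 55% to 62%
- φ = 0.5: 52% to 61%, and 53% to 65%

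The Monte Carlo standard error of each power figure is about √(0.25/1500) = 1.3 points.

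**5. Check by stratification.** Settings: Mantel-Haenszel against crude risk ratio, 48 per arm, risk ratio 1.3, 40,000 trials. Variance ratios were 1.01–1.04, 0.95–0.97, 0.85–0.89 and 0.73–0.77 at φ = 0.2, 0.3, 0.4 and 0.5. This run added half a count to the crude estimate only, which shrinks the crude variance. With 48 × 0.4 = 19.2 expected control events the factor is about (19.2/19.7)² = 0.95. The ratio of 1.01 at φ = 0.2 is therefore nearer 1.01 × 0.95 = 0.96, and the apparent loss there should not be taken literally.

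**6. Chance imbalance.** The SD of the between-arm difference in a baseline proportion p is √(2p(1 − p)/48): 0.082, 0.094 and 0.102 for p = 0.2, 0.3 and 0.5. The chance of a difference above 10 percentage points among completers is 22%, 29% and 33%. With p = 0.5 and an outcome proportion of 0.4, such a difference shifts the unadjusted risk difference by 10 × φ × √(0.24/0.25) points. That is 2.0 points at φ = 0.2 and 4.9 at φ = 0.5.

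**7. Convergence.** The log-binomial model with the added covariate failed or reached the boundary in 0.7%, 2% and 9% of simulated trials at φ = 0.3, 0.4 and 0.5.

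**The case against.** The strongest reply is that the plan follows a coherent rule. It adjusts the outcomes measured identically at baseline and follow-up (medication and IPEQ-W) and leaves unadjusted those collected only at week 5 or week 13. The unadjusted estimates are valid, and extra covariates for secondary outcomes are often settled in an analysis plan, which the protocol says will be written before unblinding. This stands as far as it shows that there is no error of validity. It does not explain why a near-identical weight-loss item should go unused when the article lists its covariates model by model and assigns the other baseline measures a descriptive role.

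A reader might go further and infer that all the week-13 behaviours and week-5 intentions have a baseline match that is being ignored. The protocol does not support that:

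- The week-13 exercise item is a less/same/more rating against the start of the study, so it is already a change and has no baseline value.
- Week-13 care seeking is four topic-specific questions covering the time since enrolment, whereas the footnote item asks "In the past month, have you seen a health professional for advice about your osteoarthritis", with no topic.
- The intentions on sedentary time, joint replacement and topic-specific care seeking have no visible counterpart.

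A reader might also infer that, because the secondary hypothesis is framed as change, an unadjusted week-13 answer cannot address it. The exercise and care-seeking items already refer back to study entry. For weight loss, a covariate sharpens the comparison but does not turn a yes/no answer into a change score.

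Finally, the added covariate does make log-binomial non-convergence more likely, most of all where the gain is largest. That objection stands and is dealt with in the fix.

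**Conclusion.** The point holds for three secondary outcomes: week-13 weight-loss behaviour, the week-5 intention to lose weight, and the week-5 intention to increase activity. It is a minor improvement. The gain is precision and protection against chance imbalance, not removal of systematic bias. Variance would fall by roughly 0% to 25% for assumed correlations of 0.2 to 0.5. With a weak correlation the gain is nil, or there is a negligible loss.

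This rests on two assumptions: that the effort items are asked at baseline, and that the correlation lies in the range shown. No sample-size figure or primary analysis changes.

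**What to change.** Before unblinding, state in the analysis plan that:

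- week-13 weight-loss behaviour and the week-5 intention to lose weight are adjusted for baseline weight-loss effort;
- the week-5 intention to increase activity is adjusted for baseline activity effort or baseline IPEQ-W, with one of the two named in advance;
- eligible joint stays in every model;
- if a log-binomial model does not converge, a robust (modified) Poisson model with the same covariates is used.

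Confirm first from the Table 2 grid that the effort items are collected at baseline. Leave the self-rated exercise change and the topic-specific care-seeking outcomes as they are, since only weak proxies exist for them.

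The cost is a few sentences in the plan and no new data. The downside is occasional non-convergence, which the fallback covers, or a negligible loss of precision if the items turn out to predict little.
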